## Abstract

**Background:**

Despite standard treatments including chemoradiotherapy with temozolomide (TMZ) (STUPP protocol), the prognosis of glioblastoma patients remains poor. AGuIX nanoparticles have a high radiosensitizing potential, a selective and long-lasting accumulation in tumors and a rapid renal elimination. Their therapeutic effect has been proven in vivo on several tumor models, including glioblastoma with a potential synergetic effect when combined with TMZ based chemoradiotherapy, and they are currently evaluated in 4 ongoing Phase Ib and II clinical trials in 4 indications (brain metastases, lung, pancreatic and cervix cancers) (> 100 patients received AGuIX). Thus, they could offer new perspectives for patients with newly diagnosed glioblastoma. The aim of this study is to determine the recommended dose of AGuIX as a radiosensitizer in combination with radiotherapy and TMZ during the concurrent radio-chemotherapy period for phase II (RP2D) and to estimate the efficacy of the combination.

**Methods:**

NANO-GBM is a multicenter, phase I/II, randomized, open-label, non-comparative, therapeutic trial. According to a dose escalation scheme driven by a TITE-CRM design, 3 dose levels of AGuIX (50, 75 and 100 mg/kg) will be tested in phase I added to standard concomitant radio-chemotherapy. Patients with grade IV glioblastoma, not operated or partially operated, with a KPS ≥ 70% will be eligible for the study. The primary endpoints are i) for phase I, the RP2D of AGuIX, with DLT defined as any grade 3–4 NCI-CTCAE toxicity and ii) for phase II, the 6-month progression-free survival rate. The pharmacokinetics, distribution of nanoparticles, tolerance of the combination, neurological status, overall survival (median, 6-month and 12-month rates), response to treatment, and progression-free survival (median and 12-month rates) will be assessed as secondary objectives. Maximum sixty-six patients are expected to be recruited in the study from 6 sites.

**Discussion:**

The use of AGuIX nanoparticles could allow to overpass the radioresistance to the reference treatment of newly diagnosed glioblastomas that have the poorest prognosis (incomplete resection or biopsy only).

**Trial registration:**

Clinicaltrials.gov: NCT04881032, registered on April 30, 2021. Identifier with the French National Agency for the Safety of Medicines and Health Products (ANSM): N°Eudra CT 2020-004552-15. Protocol: version 3, 23 May 2022.

## Background

Glioblastoma (GBM) is the most common malignant brain tumor in adults. Despite the significant improvement with the current standard treatment combining the largest possible resection, followed by concomitant radio-chemotherapy 60 Gy/30 fractions with temozolomide (TMZ) and then adjuvant chemotherapy by several cycles of TMZ [1] the prognosis of these patients remains poor. The median overall survival is 14.6 months (18.8 months, 13.5 months, and 9.4 months for patients with complete resection, partial resection, and biopsy alone, respectively) [2] and the progression-free survival at 6 months is 53.9% [1] with a poorer prognostic for the patient with unresectable GBM [2]. Moreover, GBMs are radioresistant tumors and recurrence occurs in approximately 90% of cases within the radiation fields [3]. Since there are few therapeutic solutions in case of recurrence, a radiosensitization strategy would permit to increase the chances of local control, from the first line of treatment on.

Metal nanoparticles with a high atomic number (Z) have the ability to act as radiosensitizers. They allow improving the efficiency of irradiation, by increasing the absorption of photons emitted by the radiation beam, in tumor cells. The use of nanoparticles could be a promising approach for the local treatment of tumors by external radiotherapy (RT). The radiosensitizing agent evaluated in this study is AGuIX (Activation and Guidance of Irradiation by X-ray) nanoparticles, a gadolinium chelated-polysiloxane based-nanoparticles administered intravenously [4]. This nanoparticle is a theranostic agent with very high radiosensitizing properties as well as contrast agent properties, thanks to the presence of gadolinium. The nanoparticles were tested on different orthotopic tumor models of the central nervous system (gliosarcoma [5], glioblastoma [6] and melanoma brain metastases [4]) and on mice with heterotopic tumors. Thanks to the EPR (Enhanced Permeability and Retention) effect [7], a long accumulation and retention of nanoparticles in tumor tissues is observed and they are still detectable by MRI 24 h after their intravenous administration. The nanoparticles are characterized by rapid clearance by normal tissue, high tumor-to-healthy tissue affinity ratio, with no evidence of extravasation into the brain tissue. In vivo studies have demonstrated such efficacy when combining AGuIX nanoparticles with radiation in animals with GBM [5, 8, 9] lung tumors [7], head and neck tumors [10], pancreatic tumors [11], melanoma [12] and multifocal brain melanoma metastases [4] with a survival benefit with the combination of AGuIX nanoparticles and RT, compared to RT alone. In an orthotopic glioma rat model, Dufort et al. demonstrated the selective accumulation of AGuIX in high-grade glioma as well as the potential survival benefits when combined with standard of care TMZ and radiotherapy [13].

The first-in-human phase I NANO-RAD (NCT02820454) evaluated the tolerance and the maximum tolerated dose of the intravenous injection of AGuIX nanoparticles, (15, 30, 50, 75 or 100 mg/kg) in combination with whole brain radiotherapy in patients with multiple brain metastases not suitable for stereotactic radiotherapy (from primary cancers of melanoma type *n* = 6, non-small cell lung cancer *n* = 6, colon cancer *n* = 1, and breast cancer *n* = 2). No dose-limiting toxic effects were observed up to AGuIX 100 mg/kg. This clinical trial demonstrated a good tolerance of the intravenous injection of AGuIX nanoparticles, and a rapid elimination by the kidney in correspondence with preclinical results. Among the 29 SAEs, four were considered possibly related to AGuIX and were delayed effects of RT, possibly enhanced by AGuIX [14]. Moreover, this clinical trial also demonstrated (i) the selective accumulation of AGuIX in brain metastases from different types of primary tumors due to the EPR effect, with a persistence in the tumor lasting few days after injection, (ii) a dose-correlated uptake of AGuIX in brain metastases, (iii) a dose-correlated tumor volume reduction and (iv) a clinical benefit for 13 patients over 14 when combination of AGuIX with radiotherapy [15].

Four clinical phase Ib and/or II trials are currently underway with AGuIX, with more than 100 patients already injected with AGuIX nanoparticles. The NANORAD 2 (NCT03818386) and the NANOBRAINMETS (NCT04899908) trials are randomized phase II trials evaluating the efficacy of the combination of intravenous injections of AGuIX nanoparticles (100 mg/kg) with whole brain radiotherapy or stereotactic radiosurgery/radiotherapy, respectively, in the treatment of brain metastases. The NANOSMART trial (NCT04789486) is a phase I/II trial evaluating the safety and the efficacy AGuIX in combination with stereotactic magnetic resonance-guided adaptive radiation therapy for centrally located lung tumors and locally advanced pancreatic cancers, and the NANOCOL trial (NCT03308604) is a phase Ib evaluating AGuIX in combination with radio-chemotherapy in advanced cervical cancer.

According to preclinical and clinical results, the AGuIX nanoparticles could be a promising approach to increase the effectiveness of the standard of care (TMZ and RT) in GBM patients.

Our phase I/II trial aims to test the combination of AGuIX nanoparticles with radio-chemotherapy and concomitant TMZ in patients with newly diagnosed GBM with incomplete resection.

## Methods / design

### Study design

NANO-GBM trial is a multicenter, phase I/II, randomized, open-label, non-comparative, therapeutic study.

The phase I part consists of a dose escalation with 3 dose levels of AGuIX: 50, 75 and 100 mg/kg, driven by a Time-to-event Continuous Reassessment Method (TITE-CRM) [16] with a dose-toxicity relationship given by a one-parameter power model and a priori risks of 5%, 10% and 25% for the 3 doses, respectively. The first patient will receive the first dose level, and the next cohorts will consist of 1 patient at a time, with a minimum of 6 treated at the recommended dose and a maximum of 12 patient treated in phase I.

The phase II part consists of a randomized open-label study. Patients will be randomized at baseline via a central system on eCRF, in a 2:1 ratio stratifying for the site and the age: one third of patients in the reference arm treated with radio-chemotherapy with concomitant TMZ (STUPP protocol), and two thirds in the experimental arm combining radio-chemotherapy with concomitant TMZ with the administration of AGuIX nanoparticles at the recommended dose determined in the phase I part. The randomization sequence is known only to the statistician. For the experimental arm, a single-stage Fleming design will be used. While the design does not allow for a formal comparison between the two arms, it may reinforce the value of the conclusions on the potential efficacy of the experimental treatment by validating the hypothesis on the control arm.

An interim analysis will be performed without interruption of inclusions for the independent data monitoring committee (IDMC) review, after 20 patients are treated in the experimental arm at the recommended dose (i.e. approximately 30 patients in phase II).

A maximum of sixty-six patients are expected to be enrolled: 12 patients in phase I, of which (minimum) 6 are treated at the recommended dose, 34 additional patients in the phase II experimental arm and 20 patients in the phase II reference arm. The study was started in March 2022 with a 2 years enrollment period and an estimated completion date by March 2026. This study has been registered on Clinicaltrials.gov (NCT04881032).

### Coordination and participating institutions

The Centre Jean PERRIN is the sponsor and is responsible for coordination, trial management, data management, trial monitoring and statistical analysis. This multicenter study will be conducted in 6 sites in France.

The list of the study sites is available on https://clinicaltrials.gov/ct2/show/NCT04881032

### Study objectives and endpoints

#### Mains objectives and endpoints

The primary objectives of the NANO-GBM study are i) in the phase I part, to determine the recommended dose of AGuIX in combination with radiotherapy and TMZ during the concurrent radio-chemotherapy period for phase II (RP2D); ii) in the phase II part, to estimate the efficacy of the combination radio-chemotherapy + AGuIX (at the RP2D).

The first primary endpoint (phase I) is the RP2D of AGuIX nanoparticles corresponding to the highest dose tested for which the percentage of dose-limiting toxicities (DLT) is less than 33%. DLT is defined as any grade 3–4 toxicity according to the NCI-CTCAE classification v5.0, except for alopecia, nausea and vomiting, or fever, which can be managed by symptomatic treatment. Only toxicities occurring during the concomitant radio-chemotherapy (i.e. during 6 weeks) will be considered for DLT assessment.

The second primary endpoint (phase II) is 6-month progression-free survival rate (6-month PFS) to estimate the efficacy of the combination of radio-chemotherapy with AGuIX. Disease assessment throughout the study will be based on RANO (Response Assessment in Neuro-Oncology) criteria that take into account imaging progression (MRI) and also clinical status and level of steroid therapy [17].

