### Study procedures and participant timeline

The overview of study assessments and procedures is presented in Table 2**.**

**Table 2 Tab2:** Data collection schedule

	**Screening / inclusion**		**Concomitant chemoradiotherapy phase**						**Therapeutic break**				**Adjuvant phase**							
Timepoint													**cycle 1**				**cycle 2**			
Week		**W0**	**W1**	**W2**	**W3**	**W4**	**W5**	**W6**	**W7**	**W8**	**W9**	**W10**	**W11**	**W12**	**W1 3**	**W1 4**	**W1 5**	**W16**	**W1 7**	**W18**
Day	**(-28 à -7)**	**at -7 to -3**	**0**	**7**	**14**	**21**	**28**	**35**	**42**	**49**	**56**	**63**	**70 ± 4d**	**77**	**84**	**91**	**98 ± 4d**	**105**	**112**	**119**
Informed consent	✓																			
Medical history and demographics	✓																			
Initial histology / centralized review (FFPE tumor block)	✓																			
Previous/concomitant treatments (including corticosteroids)	✓		throughout the treatment																	
Evaluation of adverse events			throughout the treatment																	
Radiological evaluation MRI (disease)	✓(according to standard practice)												✓							
MRI dosimetry	✓(-15 à -5)																			
MRI post injection AGuIX (1 h after injection)^h^		✓^**h**^			✓^**h**^															
Examination neurological (MMSE)	✓												✓							
Clinical examination, weight	✓	✓^**h**^	✓	✓	✓	✓	✓	✓					✓				✓			
Vital signs^a^	✓	✓^**h**^	✓	✓	✓	✓	✓	✓					✓				✓			
KPS Performance Index	✓	✓^**h**^	✓	✓	✓	✓	✓	✓					✓				✓			
Serum pregnancy test^g^	✓				✓			✓					✓				✓			
Hematology^b^	✓	✓^**h**^	✓	✓	✓	✓	✓	✓					✓				✓			
Fasting biochemistry^c^	✓	✓^**h**^	✓	✓	✓	✓	✓	✓					✓				✓			
Urine analysis^d^	✓	✓^**h**^	✓	✓	✓	✓	✓	✓					✓				✓			
Pharmacokinetics^f^			✓^f^	✓^f^	✓^f^															
Radiotherapy			**2 Gy**** x 5d / week pour 6 weeks**																	
Temozolomide			**75 mg/m**^**2**^** daily intake D0 à D42**										**5D**^**e**^				**5D**^**e**^			
AGuIX (injection IV)^i^		**D-7 to D- 3**^**j,h**^	**D0**^**h**^	**D7**^**h**^	**D14**^**h**^															
survival assessment			throughout the study																	

	**Adjuvant phase**																**End of treatment visit**	**Follow-up to progression**	**Follow-up of survival**
Timepoint	**cycle 3**				**cycle 4**				**cycle 5**				**cycle 6**					**every 3 months for 18 months after V(W35) then every 6 months**	**every 3 months for 18 months after V(W35) then every 6 months**

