Week	**W19**	**W20**	**W21**	**W22**	**W23**	**W24**	**W25**	**W26**	**W27**	**W28**	**W29**	**W30**	**W31**	**W32**	**W33**	**W34**	**W35**		
Day	**126 ± 4d**	**133**	**140**	**147**	**154 ± 4d**	**161**	**168**	**175**	**182 ± 4d**	**189**	**196**	**203**	**210 ± 4d**	**217**	**224**	**231**			
Informed consent																			
Medical history and demographics																			
Initial histology / centralized review (FFPE tumor block)																			
Previous/concomitant treatments (including corticosteroids)																			
Evaluation of adverse events																			
Radiological evaluation MRI (disease)					✓												✓	✓	
MRI dosimetry																			
MRI post injection AGuIX (1 h after injection)^h^																			
Examination neurological (MMSE)					✓												✓	✓	
Clinical examination, weight	✓				✓				✓				✓				✓	✓	
Vital signs^a^	✓				✓				✓				✓				✓		
KPS Performance Index	✓				✓				✓				✓				✓	✓	
Serum pregnancy test^g^	✓				✓				✓										
Hematology^b^	✓				✓				✓				✓				✓		
Fasting biochemistry^c^	✓				✓				✓				✓				✓		
Urine analysis^d^	✓				✓				✓				✓				✓		
Pharmacokinetics^f^																			
Radiotherapy																			
Temozolomide	**5D**^**e**^				**5D**^**e**^				**5D**^**e**^				**5D**^**e**^						
AGuIX (injection IV)^i^																			
survival assessment																			✓

^a^vital signs include heart rate measurement, systolic and diastolic blood pressure, temperature, pulse

^b^hemoglobin, CBC platelet

^c^glucose, sodium, potassium, magnesium, calcium, total protein, creatinine, urea, AST, ALT, alkaline phosphatase, GGT, total bilirubin

^d^proteinuria

^e^TMZ 150—200 mg/m^2^/d D1 at D5 every 28 days (the daily dose of 150 mg/m^2^ for the first cycle will be increased to 200 mg/m^2^ for the 2nd cycle in the absence of significant toxicity)

^f^pharmacokinetics performed only for phase I patients: blood sampling 7 ml before injection, 15 min, 30 min, 1 h (before MRI), 2 h, 3 h, 4 h (before the beginning of radiotherapy), 6 h and 24 h post injection + urine collection during 6 h

^g^for patients of childbearing age

^h^only for patients receiving the experimental treatment: Phase I + Phase II experimental arm

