### Statistical analysis

#### Sample size

A maximum of 12 patients will be treated in phase I (sample size obtained by simulation, and in agreement with the bound obtained by Cheung’s formula, 2013), minimum 6 patients to be treated at the recommended dose, who will then be included and analyzed in phase II.

The phase II trial consists of a randomized study with a 2:1 ratio in favor of the experimental arm. For the experimental arm, a single-stage Fleming design will be used, based on an acceptable success rate of 70% and a 50% unacceptable success rate. In order to limit the one-sided alpha risk (of wrongly concluding that the treatment is effective) to 5% and the beta risk (of wrongly failing to conclude that the treatment is effective) to 20%, the minimum number of patients to include is 37. The treatment will be considered effective (and therefore the phase II positive) as soon as 24 successes out of 37 are obtained. In this case, the estimate of the probability of success will be of around 65%, with a 90% confidence interval (90% CI) of 51.4%-76.7% (Jeffreys interval).

It was decided to include 40 patients in the experimental arm, to compensate for a rate of about 10% of missing data (all reasons combined). Therefore, the number of patients in the reference arm will be 20.

Consequently, the total number of patients to be included is 66 (maximum): 12 patients in phase I, of which (minimum) 6 were treated at the recommended dose, 34 additional patients in the experimental arm of phase II, and 20 patients in the reference arm of phase II.

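### No disease MRI is scheduled at month 6, so the 6-month PFS rate tested against 50% can be biased upward and the 5% false-positive limit may be exceeded

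*Protocol article*

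**What the plan says.** Under Mains objectives and endpoints, the article states: "The second primary endpoint (phase II) is 6-month progression-free survival rate (6-month PFS"). Progression follows RANO criteria, which "take into account imaging progression (MRI) and also clinical status and level of steroid therapy".

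In Table 2 (Study procedures and participant timeline), the row "Radiological evaluation MRI (disease") is ticked at screening, W11 (D70), W23 (D154 ± 4 days) and W35. The day cell for W35 is blank; W34 is D231, so W35 is about D238. Follow-up to progression then runs "every 3 months for 18 months after V(W35) then every 6 months". The W27 visit (D182 ± 4 days) has clinical examination and KPS ticked, but not disease MRI.

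The article gives no time origin for PFS. Under Study design, "Patients will be randomized at baseline via a central system on eCRF"; Table 2 puts screening and inclusion between D-28 and D-7.

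Under Sample size, the experimental arm uses a single-stage Fleming design "based on an acceptable success rate of 70% and a 50% unacceptable success rate", with one-sided alpha 5% and beta 20%, N = 37, and a positive result at 24 successes. Under Data analysis, PFS rates are estimated by Kaplan–Meier, and the 6-month rate in the experimental arm is read by the Fleming method.

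**The concern.** Month 6 counted from D0 is D182 to D183. It lies inside a 12-week interval with no scheduled disease imaging (D154 to about D238). On the usual convention, an event is dated at the assessment that shows it. A tumour that progresses on imaging alone between D154 and month 6 then enters the Kaplan–Meier curve at about D238, and the patient is a success at month 6. Scheduled imaging cannot produce an error in the other direction.

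The phase II conclusion rests on one count compared with a fixed 50%. If ineffective treatment can yield more than 50% recorded successes because of the scan calendar, the trial can be declared positive more often than the stated 5%.

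**Working it through.** **1. The plan's own figures.** With X binomial (n = 37), P(X ≥ 24 | 0.50) = 0.0494 and P(X ≥ 24 | 0.70) = 0.807. N = 37 with cut-off 24 is the smallest design meeting both limits, so the stated design reproduces. Alpha is only 0.0006 below its limit.

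**2. The calendar.** Six months = 6 × 30.4375 = 182.6 days. From D0, the W23 scan falls at 154/30.4375 = 5.06 months and W35 at 238/30.4375 = 7.82 months. The W23 scan precedes month 6 by 182.6 − 154 = 28.6 days. If PFS starts earlier, the scan moves towards the landmark: 5.29 months from D-7, 5.52 from D-14, 5.75 from D-21 and 5.98 from D-28.

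**3. Assumptions.** True 6-month PFS is 50% and the hazard is constant. A share f of progressions between the W23 scan and month 6 goes unseen until W35. The 50% reference is free of a similar delay. With the origin d days before D0:

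- S = 0.5^((154 + d)/182.6) is true PFS at the W23 scan
- p = 0.5 + f × (S − 0.5) is the recorded 6-month success rate
- false-positive rate = P(X ≥ 24 | 37, p)

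**4. Results.**

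| Origin | S at W23 scan | f = 1 | f = 0.5 | f = 0.25 |
|---|---|---|---|---|
| D0 | 0.557 | 0.171 | 0.097 | 0.070 |
| D-7 | 0.543 | 0.129 | 0.082 | 0.064 |
| D-14 | 0.529 | 0.096 | 0.070 | 0.059 |
| D-21 | 0.515 | 0.071 | 0.059 | 0.054 |
| D-28 | 0.501 | 0.051 | 0.050 | 0.050 |

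With f = 0 the rate is 0.049 for every origin. In the D0, f = 1 cell the excess is 37 × (0.557 − 0.50) ≈ 2 successes.

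**5. Sensitivity of that extreme cell.** The ± 4-day visit window gives 0.146 (D158) to 0.199 (D150). Replacing the constant hazard by a Weibull gives 0.138 for shape 0.8 and 0.269 for shape 1.5.

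**The case against.** Four points on the other side have force.

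- **Detection without a scheduled MRI.** RANO progression also uses clinical status and steroid dose, corticosteroids are recorded throughout treatment, the D182 visit includes clinical examination and KPS, deaths are dated as they occur, and unscheduled scans are not excluded. A reader might infer that the endpoint is in truth PFS at about five months. The documents do not support that: it needs f = 1 and an origin at D0 together.
- **Origin.** Randomisation at baseline suggests an origin before D0, which shrinks the problem and nearly removes it at D-28. The full protocol may define the origin; an article often does not. This stands as a limit on the size.
- **The reference rate.** A reader might infer that inflation of the false-positive rate is proven. It is not. The article cites a historical 6-month PFS of 53.9% without its scan schedule and does not say how 50% was derived. If the reference carried a similar delay, the bias would largely cancel.
- **The control arm.** It has the same disease MRI schedule and is meant to check the control hypothesis, so it would share the upward shift. This helps only a little: with 20 patients the standard error at 50% is √(0.25/20) = 0.11, about twice the largest shift in the table (0.057), and no formal comparison is planned.

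The mismatch and its direction survive. The size becomes a range.

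**Conclusion.** The point holds in a limited form. It is certain that no disease MRI is scheduled at the landmark of the phase II primary endpoint, and that imaging-only progressions after the W23 scan and before month 6 would be recorded late. The rate compared with 50% can therefore be biased upward.

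Under a constant hazard, a true rate of 50% and an undelayed reference, the chance of a false positive lies between about 5% and 17%, with 7 to 10% in intermediate cases, against a stated 5%. Where the trial falls in that range depends on the PFS origin, the share of late progressions found without a scheduled scan, and the imaging behind the 50%. The article gives none of these. The point deserves correction because it bears on the only phase II decision rule, but it does not show that the rule fails.

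**What to change.** **Preferred.** State the PFS origin, and reconcile the imaging schedule with the endpoint by aligning one already planned disease MRI with the month-6 visit in both arms. This adds no scan but needs an amendment. Moving the W23 scan to D182 would stretch the interval since the D70 scan from 84 to 112 days; whether that is acceptable is for the investigators to judge.

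**If the schedule is kept.** Treat progression as interval-censored, and report the 6-month rate with a conservative bound that counts imaging-only progressions first seen at W35 as 6-month failures. Show the Fleming conclusion under both datings, and check the 50% assumption in the control arm under the same dating. The bound is needed because, with scans only at D154 and about D238, the data alone cannot place an imaging-only event within that interval.

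The cost is power. Take true 6-month PFS of 70%, constant hazard and origin D0: PFS at D238 is 0.7^(238/182.6) = 0.628. If half of the D154–D238 progressions are imaging-only, the conservative success rate is 0.70 − 0.5 × (0.70 − 0.628) = 0.664, and P(X ≥ 24 | 37) is 0.65 instead of 0.81. If all are, it is 0.47.

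**Not advised.** Resetting the cut-off as if the endpoint were read at D154, for example to 28 of 40. That is tuned to the extreme case (alpha 0.047 at 0.557, power 0.78 at 0.740). If half of the late progressions are found clinically, power at a true 70% falls to 0.68 and alpha to 0.02; with the origin at D-28, power is 0.58.
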